##### TMS-derived measures of cortical excitability

Two researchers and a neurologist, blinded to group allocation, will be responsible for recording bilateral TMS-EMG data to establish stimulation parameters for the iTBS intervention and determine cortical excitability measures.

Surface EMG data will be recorded after a contralateral single-pulse TMS of the FDI muscle with disposable pregelled Ag/AgCl electrodes (EL503, BIOPAC Systems, Inc., California, United States) in a tendon-belly arrangement. Each participant’s skin will be cleaned with a 70% isopropyl alcohol swab to reduce impendences (<5 kΩ) related to skin conductance.

EMG data will be collected using an EMG amplifier and recorded using a BrainAmp ExG amplifier (Brain Products GmbH, Gilching, Germany). For visual display, we will use some filters (bandpass filter: 10–1,000 Hz, sampling rate: 1 kHz) to remove low-frequency artifacts that occur during stimulation; however, raw data will be recorded. All these measures will be visualized and recorded using BrainVision Recorder 2.1 software (Brain Products GmbH, Gilching, Germany).

For EMG analysis, data will be filtered (bandpass filter of 20 Hz to 450 Hz) and digitized at a rate of 1 Hz. The notch filter will be set at 50 Hz to remove power line interference. Different parameters will be obtained from the electromyography session using Analyzer 2.1.2 software (BrainVision Analyzer, Brain Products GmbH, Gilching, Germany) and custom routines and MATLAB toolboxes.^2^ Subsequently, data will be segmented by markers to delimitate trials. In our case, each single TMS pulse will be a marker. Subsequently, baseline correction and artifact rejection will be performed. Normalized EMG data will be used for subsequent statistical analysis.

The following TMS-EMG parameters of cortical excitability will be obtained after stimulation of the FDI muscle hotspot of the mapping grid:

The resting motor threshold (rMT) of the relaxed FDI muscle will be determined by the modified relative frequency method, under which the rMT is defined as the minimum stimulation intensity required to produce a peak-to-peak MEP amplitude ≥50 μV in at least five out of ten consecutive trials when single pulses are applied to the target area and while the patient is in a resting state (Rossini et al., 1994).The active motor threshold (aMT), which is defined as the minimum stimulation intensity needed to produce a peak-to-peak MEP amplitude of 200 μV from the contralateral FDI muscle in 50% of the trials when ten consecutive single pulses are applied with the TMS while the patient is actively contracting the target muscle (20% of maximal voluntary contraction, as determined by visual feedback; Rothwell et al., 1999; Huang and Rothwell, 2004). The 80% stimulation intensity threshold for the aMT will be used to determine parameters for iTBS treatment (Huang et al., 2005).To ameliorate the impact of the variability in cortical excitability parameters such as MEP amplitude and MEP onset (Rossini et al., 1994), twenty single pulses (“20 t”) with an interpulse interval of 4–5 s will be given at the minimum intensity able to evoke 1 mV peak-to-peak MEPs in five out of ten consecutive trials from the relaxed contralateral FDI muscle (Bagnato et al., 2006; Suppa et al., 2014)The cortical silent period (cSP) will be determined by recording 10 single pulses separated by 10 interpulse seconds and delivered at an intensity of 140% of the rMT while the patient is maintaining a constant voluntary contraction of the contralateral FDI muscle (at 20% of maximal voluntary contraction, as determined by visual feedback; Farzan, 2014).

Aside from these motor threshold values, cortical excitability analysis will include the integration and examination of multiple parameters obtained from the 20 t and cSP recordings. For the analysis of the 20 t trials, a visual inspection will be performed to reject MEPs considered to be outliers. Considering the large fluctuation in amplitude response when recording a cascade of MEPs with a threshold intensity (Rossini et al., 1994), motor evoked potentials will be discarded when their peak-to-peak amplitude is <200 μV. From the 20 t recording, a total of three parameters will be obtained: MEP onset, peak-to-peak amplitude, and MEP area.

MEP onset (ms): defined as the time between the application of a single TMS pulse and the change of the constant EMG baseline with increasing amplitude. For the determination of the 20 t MEP onset, the lowest latency from the most representative group of onsets of all twenty trials will be selected (Groppa et al., 2012).Peak-to-peak amplitude (mV): defined as the average distance between the maximum positive peak and the maximum negative peak in the waveform of the total plotted MEPs.MEP area (μV/ms): defined as the area under the rectified MEP curve counting from onset to the offset previously established for the non-rectified averaged MEP. Thus, MEP Area onset will be defined as the beginning of the MEP, and offset will be defined as the return of MEP activity to baseline.

For the cSP recording, a total of five measures will be calculated: cSP duration, MEP peak-to-peak amplitude, MEP area, cSP ratios (duration/amplitude and duration/area; Orth and Rothwell, 2004). A visually guided manual method will be used for inspection. Mean cSP values will be plotted based on trial-by-trial measurements.

Absolute cSP duration (ms): average duration from the MEP offset to the resumption of sustained EMG activity. The resumption of EMG activity determines the end of cSP (Orth and Rothwell, 2004; Oliviero et al., 2005, 2006; Groppa et al., 2012; Farzan, 2014).MEP amplitude: mean peak-to-peak amplitude of the MEPs before the cSP.MEP area: area under the rectified MEP curve (Orth and Rothwell, 2004).cSP ratio I: calculated as cSP duration/MEP amplitude (Orth and Rothwell, 2004; Oliviero et al., 2006).cSP ratio II: calculated as cSP duration/MEP area (Orth and Rothwell, 2004).

Finally, rMT, aMT, 20 t and cSP values will be entered in a database and subsequently analyzed in SPSS.

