Motor mapping will be performed on a 3 × 3 mm grid above the motor hand area. The center of the grid will be located on the central point of the hand-knob structure such that this area and possible error range are fully covered. For hotspot identification, the central point of the grid will be used for the determination of the minimum suprathreshold intensity that elicits a peak-to-peak MEP > 50 μV for three consecutive trials in the resting state. Subsequently, one TMS pulse will be given at each spot of the grid at 110% of this established intensity. The optimal location or hotspot will be determined as the grid position with the largest amplitude and the shortest latency that provokes movement in the FDI muscle. If these two parameters are not in the same spot, the optimal location will be defined according to the largest amplitude (Charalambous et al., 2019). If no neuroimaging images are available or hotspot identification is not successful after grid mapping, the 10/20 system C1/C2 will be used to locate the motor hand area, which has been demonstrated to offer a more accurate position for the motor hand area than C3/C4 (Silva et al., 2021; Kim et al., 2023). Visually guided and neuronavigated manual mapping will be performed to identify the location of the FDI muscle hotspot. This process will be replicated for both hemispheres.

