Although the postulated mechanism of iTBS (i.e., stimulating neuronal and glial activity) has been demonstrated to prompt LTP-like plasticity *in vivo* (Funamizu et al., 2005; Cullen and Young, 2016; Cacace et al., 2017), human studies targeting microglia and astrocyte reactivity in areas affected by neurological or psychiatric diseases are scarce. Thus, it has been hypothesized that the benefits of iTBS for reducing motor and nonmotor symptomatology in patients with PD, as well as many other brain-related diseases, might be due to effects on microglia and astrocytes, which play a protective role in neurodegenerative and neuroinflammatory diseases (Stanojevic et al., 2022). In line with the quantification of blood biomarkers of neurodegeneration, some recent studies have reported that excitatory frontal and parietal rTMS, in addition to improving cognition, is not associated with neuroaxonal damage or neurodegeneration in healthy populations according to plasma NfL concentrations (Redondo-Camós et al., 2022); thus, the effects of iTBS on reducing neurodegenerative pathology in animal models and humans still need to be tested. Furthermore, evidence from animal models and neurological patients suggests that TBS and rTMS protocols may induce changes in the regulation of BDNF expression (Zhang et al., 2007; Stevanovic et al., 2019) or changes in BDNF protein levels (Müller, 2000) and promote neuroprotection and neuroplasticity (Feng et al., 2012; Castillo-Padilla and Funke, 2016; Zuo et al., 2020). However, the role of BDNF in the effects of TBS on PD patients is still debated, as it may have a variable response to iTBS compared to cTBS, likely because the PD brain might be less susceptible to iTBS-induced motor plasticity and potentiation (Cheeran et al., 2008). Further investigation of BDNF down/upregulation is essential to better understand the scope and capacity of iTBS-induced plasticity.

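### Discarding 20 t MEPs below 200 μV before averaging selects trials on the outcome itself and biases 20 t amplitude, by an amount that depends on trial spread the article does not give

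*Protocol article*

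**What the plan says.** In the section on TMS-derived measures of cortical excitability, the 20 t recording is twenty single pulses to the relaxed FDI muscle. The intensity is the lowest that evokes 1 mV in five of ten trials. Twenty pulses are used to reduce the effect of variability in MEP amplitude and onset.

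Two rejection steps follow. First, "a visual inspection will be performed to reject MEPs considered to be outliers"; the article gives no numeric criterion for this. Second, with the reason "Considering the large fluctuation in amplitude response when recording a cascade of MEPs with a threshold intensity", a fixed limit applies: "motor evoked potentials will be discarded when their peak-to-peak amplitude is <200 μV". No numeric upper limit is given. Artefact rejection has already been listed earlier in the same section, as part of EMG processing. Peak-to-peak amplitude is then defined as an average over the plotted MEPs.

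Other amplitude criteria in the article are:
- rMT, relaxed muscle: "the minimum stimulation intensity required to produce a peak-to-peak MEP amplitude ≥50 μV in at least five out of ten consecutive trials".
- Hotspot search, relaxed muscle (section on TMS intervention and neuronavigation): "elicits a peak-to-peak MEP > 50 μV for three consecutive trials in the resting state".
- aMT, contracting muscle: "minimum stimulation intensity needed to produce a peak-to-peak MEP amplitude of 200 μV from the contralateral FDI muscle in 50% of the trials".

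Table 1 lists TMS-EMG cortical excitability as a secondary outcome. The statistical analysis section puts TMS-EMG parameters at the centre of the correlation analyses, and significant correlations go on to stepwise regression.

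**The concern.** A rule that deletes observations because the outcome is low changes what the average estimates. It becomes the mean amplitude of those responses that reached 200 μV, not the mean response to the stimulus. The share deleted depends on how excitable the cortex is at that visit, so the distortion differs between baseline and post-treatment and, if iTBS works, between real and sham.

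The stated reason does not call for the rule. Averaging twenty trials already deals with fluctuation and adds no bias, whereas cutting only the low tail does add bias. Artefacts have their own rejection step.

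What is at stake is the change in 20 t amplitude between visits and conditions, and the correlations and regressions that use it.

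**Working it through.** The article gives no figure that depends on this rule, so there is nothing to reproduce. The check compares the full mean with the mean of the trials that survive the cut-off.

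**Inputs**
- Cut-off c = 0.2 mV, from the article.
- Baseline single-trial median of 1 mV, read from the 20 t intensity definition (1 mV in five of ten trials).
- Log-normal trials with log-SD s from 0.6 to 1.0. This is an assumption; the article gives no single-trial spread.
- The same stimulus intensity before and after iTBS. This is also an assumption; the article does not say whether the intensity is held or reset.

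**Formulas.** With median m and a = (ln c − ln m)/s:
- share discarded = Φ(a)
- full mean = m·exp(s²/2)
- mean after the cut-off = full mean × Φ(s − a)/Φ(−a)

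**Worked example, s = 1.0**
- m = 1: a = ln 0.2 = −1.609. Discarded: 5.4%. Full mean 1.649 mV; after the cut-off 1.649 × 0.9955/0.9462 = 1.735 mV.
- m = 0.5: a = −0.916. Discarded: 18.0%. Full mean 0.824 mV; after the cut-off 0.824 × 0.9723/0.8202 = 0.977 mV.
- True change −50%. Observed change 0.977/1.735 − 1 = −43.7%.

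**Pure shift at constant spread** (each range runs from s = 0.6 to s = 1.0)

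| Median after iTBS | Trials lost | True change | Observed change |
|---|---|---|---|
| 1.0 mV | 0.4% to 5.4% | 0 | 0 |
| 1.3 mV | 0.1% to 3.1% | +30% | +29.7% to +27.2% |
| 0.5 mV | 6% to 18% | −50% | −47.7% to −43.7% |

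**Sensitivity to the assumed distribution.** With narrow log-normal spread (s = 0.3), at least 98% of the absolute change is kept even for a fall to 0.3 mV. With normal trials, mean 1 mV and SD 0.5 to 0.6 mV, 65% to 75% of a fall to 0.7 or 0.8 mV is kept, and 78% to 90% of a rise to 1.25 or 1.5 mV. The effect therefore runs from negligible to about a third of the change.

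**When more than location changes**
- Median 1 to 0.6 mV with s 0.5 to 1.05: the true mean goes from 1.133 to 1.041 mV (−0.092). After the cut-off it goes from 1.134 to 1.200 mV (+0.066). The sign is reversed.
- Median fixed at 1 mV with s 0.5 to 0.9: true change +0.366 mV, observed +0.417 mV. The change is inflated.
- Four of twenty trials stay at 0.1 mV and sixteen rise from 1.0 to 1.3 mV: the true change is (16 × 0.3)/20 = +0.24 mV. After the cut-off it is +0.30 mV, again inflated.

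These last cases are constructed to show that the direction of the bias is not guaranteed. They do not predict what this trial will see.

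**The case against.** The strongest reply is that the effect is trivial in the direction the trial expects. The article describes iTBS as excitatory. Under the log-normal assumption about one trial in twenty or fewer is lost at 1 mV (0.054 × 20 = 1.1), and a 30% rise is almost fully preserved. The same rule applies to both conditions and all visits. If the 20 t intensity is reset to 1 mV after iTBS, amplitude is held near its target by design and large falls would not arise. The article also says that normalized EMG data will be analysed, without saying how, so raw millivolt means may not be the final scale. All of this stands as a limit on size. It does not make a one-sided, outcome-dependent deletion sound, because equal application of the rule does not give equal loss when excitability differs.

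Three stronger readings are tempting, and the documents do not support them.
- A reader might infer that every change is pulled towards zero. That holds only for a shift at constant spread, as the counterexamples show.
- A reader might see a contradiction with the 50 μV criterion ("peak-to-peak MEP amplitude ≥50 μV in at least five out of ten consecutive trials"). That figure is for finding a threshold or a hotspot, and the article never states it as a validity limit for 20 t trials. It shows only that smaller resting MEPs are treated as real responses elsewhere.
- A reader might take the Discussion's remark that "the PD brain might be less susceptible to iTBS-induced motor plasticity and potentiation" as evidence that amplitudes will fall by half or more. It suggests a weaker rise or none. The 50% fall above is illustrative only.

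**Conclusion.** The point holds in a limited form. The cut-off selects 20 t trials on the measured value from the low side, raises the mean, and removes more trials where excitability is lower. With a pure shift and fixed intensity the change is attenuated: slightly for modest facilitation and by a few percentage points for a halving, under log-normal trials with log-SD 0.6 to 1.0. Other assumed distributions give anything from almost no effect to a loss of about a third. If spread or trial mix changes, the direction cannot be relied on.

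The scope is narrow: 20 t amplitude within a secondary outcome, and the correlation and regression analyses that use it. The primary MDS-UPDRS outcome, the sample size, rMT, aMT and the cSP measures are not touched. This is a cheap improvement, not a threat to the trial's main conclusion.

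**What to change.** Remove the 200 μV cut-off from the main analysis. Average all 20 trials except those rejected for artefact or muscle pre-activation by a rater blind to condition and time point. Report the number of trials below 200 μV per visit and condition, and show the truncated average only as a sensitivity analysis. State whether the 20 t intensity is held at its baseline value or reset after iTBS, since the meaning of an amplitude change depends on it. The onset definition, which refers to the full set of twenty trials, would then agree better with the amplitude rule.

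This changes only an analysis rule. Raw EMG is recorded, so no patient visit or new measurement is needed, and patients already enrolled can be reprocessed in the same way. The downside is slightly more trial-to-trial variance from small responses.

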#### Structural and resting-state functional MRI

Structural and functional MRI analyses will be conducted by two experienced imaging scientists with solid knowledge of advanced volumetric and surface structural procedures and resting-state functional connectivity (rs-FC) analysis. After the MRI data are collected, images will be converted into NIfTI format. Subsequently, a visual inspection will be performed for the detection of artifacts, and they will be manually aligned along the anterior and posterior commissure (AC & PC) with Statistical Parametrical Mapping (SPM12).^3^ Four different analyses will be performed to examine cerebral structural and functional integrity.

Gray matter (GM) volume quantification will be obtained following voxel-based morphometry (VBM) methods using the Computation Anatomy Toolbox (CAT-12, version 12.7) with the current version of SPM12. For this purpose, 3D T1-weighted images will first be visually inspected for artifacts. Subsequently, preprocessing will be performed following standard steps suggested in the CAT-12 manual: (1) bias-field correction; (2) segmentation into GM, white matter (WM), and cerebrospinal fluid (CSF); (3) registration to a standard template using the DARTEL algorithm; (4) normalization of GM images to the Montreal Neurological Institute (MNI) template; and (5) modulation and smoothing of normalized data using an 8 mm FWHM Gaussian kernel. GM volumes of cortical regions of interest will be extracted and corrected for total intracranial volume using the Neuromorphometrics atlas.^4^

Cortical thickness (CT) computation will be obtained using the CAT-12 toolbox, which follows an automated method of tissue segmentation based on the estimation of distances between WM and GM voxels using a projection-based thickness method, including topology correction and spherical mapping. Additionally, individual cortical surface maps will be smoothed with a 15 mm Gaussian kernel to allow intersubject comparisons. Regional CT values will be extracted using the Desikan-Killiany atlas (Desikan et al., 2006).

Independent component analysis (ICA) of rs-FC data. Resting-state fMRI images will be preprocessed using the Data Processing & Analysis for Brain Imaging tool (DPARSF V4.3).^5^ Preprocessing will include removal of the 10 first functional volumes, slice-timing correction, realignment of the first volume, coregistration, segmentation, spatial normalization to MNI space and spatial smoothing (with a 4-mm FWHM Gaussian kernel). Furthermore, ICA will include the estimation and extraction of brain networks of interest following the infomax algorithm, performed with the Group ICA toolbox of fMRI Toolbox (GIFT) software.

Seed-based rs-FC. Resting-state fMRI data will be preprocessed using the Data Processing & Analysis for Brain Imaging tool (DPARSF V4.3; footnote 5). Preprocessing will include removal of the 10 first functional volumes, slice-timing correction, realignment to the first volume, head-motion correction, coregistration, nuisance covariate regression, spatial normalization to MNI space, spatial smoothing (with a 4-mm FWHM Gaussian kernel), and temporal filtering (0.01 Hz – 0.1 Hz). Seed-to-voxel and seed-to-seed FC values will be computed. The brain regions with significant structural differences between the real and sham iTBS conditions will subsequently be used as seeds to trace the brain regions associated with abnormal FC.

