### Procedure and intervention

Our study will be composed of 2 different phases, Phase I and Phase II, separated by a washout period of at least 3 months. Each phase will consist of 3 stages: baseline evaluation, iTBS intervention, and posttreatment evaluation (Figure 1). The baseline evaluation period will begin once the patients agree to participate in the investigation. From this moment until a maximum of 30 days later, patients will undergo (i) a clinical and motor examination in the ON state, (ii) an extensive cognitive and neuropsychiatric assessment, (iii) a resting-state EEG recording, (iv) structural and functional MRI scans, and (v) blood sample collection. Moreover, immediately following the completion of baseline evaluations and just prior to the start of the iTBS intervention stage, a variety of TMS-EMG cortical excitability measures will be acquired. Once this first stage is fully completed, patients will receive a session of real or sham iTBS over the bilateral M1 once per day for five consecutive days. During the last session of iTBS, TMS-EMG parameters of cortical excitability will be acquired, and patients will undergo a clinical motor evaluation. After the intervention stage, the posttreatment evaluations will be conducted. Subsequently, within a 3–4 day window, resting-state EEG data will be recorded for all participants. A week after the last iTBS session, patients will undergo a second clinical evaluation, and a new blood sample will be collected. Next, on the eighth day posttreatment, structural and functional MRI scans will be acquired. At 2 weeks post-iTBS, a new neuropsychiatric and cognitive assessment will be performed along with a third motor evaluation. Finally, the last visit will occur 28 days after the iTBS intervention, consisting of the fourth and final clinical evaluation (Figure 1). Subsequently, all patients will undergo a washout period of at least 3 months prior to the start of the crossover process and Phase II of the study.

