### Outcome measures

Participants will undergo an extensive assessment of seven areas of interest: basic demographic information, clinical and motor assessment, TMS-EMG parameters of cortical excitability, cognitive and neuropsychiatric evaluations, electrophysiology and neuroimaging examination, and serum biomarker testing. Each measure will be collected before and after treatment for both the real and sham groups and during the two phases of the study. Primary, secondary, and exploratory outcome measures are summarized in the Table 1.

**Table 1 tab1:** Primary, secondary, and exploratory outcome measures.

	Measure	Domain measured

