**Exploratory outcomes**		
Electrophysiology	Resting-state EEG activity	EEG PSD and connectivity measures, synchronization measures from graph theory metrics.
Neuroimaging	Structural MRI - T1-weitghted (T13D)	Global and regional GM volume changes and CT computation changes
	Resting-state fMRI	Seed-to-voxel and seed-to-seed functional connectivity measures
Serum protein quantification	Single-molecule assay (Simoa; SR-X™ biomarker detection system)	NfL levels
		GFAP levels
		BDNF levels

aMT, active motor threshold; BDI-II, beck depression inventory; BDNF, brain-derived neurotrophic factor; BVRT, Benton visual retention test; CNS-LS, center for neurology study-lability scale; cSP, contralateral silent period; CT, cortical thickness; EEG, encephalography; EMG, electromyography; FAB, frontal assessment battery; fMRI, functional magnetic resonance imaging; FrSBe, frontal systems behavior scale; GFAP, glial fibrillary acidic protein; GM, gray matter; HAM-A, Hamilton anxiety rating scale; LEDD, levodopa equivalent daily dose; MDS-UPDRS, the movement disorder society-sponsored revision of the unified Parkinson’s disease rating scale; MMP, mini mental Parkinson; MRI, magnetic resonance imaging; NfL, neurofilament light chain; PD, Parkinson’s disease; PDQ-39, Parkinson’s disease questionnaire; PFS-16, Parkinson fatigue scale; PPQ, Parkinson’s psychosis questionnaire; PSD, power spectral density; QUIP, questionnaire for impulsive-compulsive disorders in Parkinson’s disease; rMT, resting motor threshold; SAS, Starkstein apathy scale; SEND-PD, scale for the evaluation of neuropsychiatric disorders in Parkinson’s disease; TMS, transcranial magnetic stimulation.

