#### Neuroimaging

For all participants, brain MRI data will be collected using a 1.5 T scanner (Siemens Symphony, Erlangen, Germany). The following sequences will be used for data acquisition:

Structural MRI: high-resolution T1-weighted anatomical images will be obtained using a 3D sagittal MPRAGE sequence (TR = 2.200 ms, TE = 3 ms, flip angle = 8°, matrix = 384 × 512 × 176, voxel size = 0.5 × 0.5 × 1 mm).Resting-state fMRI: a T2-weighted functional echo-planar imaging (EPI) sequence sensitive to blood oxygen level-dependent (BOLD) signals will be performed with the following parameters during the eyes-open resting state: repetition time/echo time = 3.000 ms/50 ms, 49 ascending slices, matrix = 64 × 64 × 49, voxel size: 4.06 × 4.06 × 4.05. A total of 120 volumes will be acquired with each scan lasting approximately 7 min.

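### The structural MRI outcomes are short-term changes within a patient, but the listed processing steps name no alignment of a patient's own T1 scans to each other

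*Protocol article*

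**What the plan says.** All places are in the protocol article.

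- **Outcome.** Table 1, under exploratory outcomes, defines the structural measure as "Global and regional GM volume changes and CT computation changes".
- **Scans.** Outcome measures states: "Each measure will be collected before and after treatment for both the real and sham groups and during the two phases of the study". Procedure and intervention fixes the later scan: "Next, on the eighth day posttreatment, structural and functional MRI scans will be acquired". A patient who completes both phases therefore has four T1 scans, two per phase. All are taken at 1.5 T (Neuroimaging).
- **Volume.** In Structural and resting-state functional MRI, images are first aligned by hand to the commissures. The section then says "preprocessing will be performed following standard steps suggested in the CAT-12 manual" and numbers five steps. Bias correction and segmentation come first, followed by "3) registration to a standard template using the DARTEL algorithm; (4) normalization of GM images to the Montreal Neurological Institute (MNI) template", then modulation and 8 mm smoothing.
- **Thickness.** The same section says that "individual cortical surface maps will be smoothed with a 15 mm Gaussian kernel to allow intersubject comparisons". It does not say how repeat scans of one patient are brought together.
- **Later use.** For seed-based connectivity, the seeds are the regions that differ structurally between the real and sham conditions.

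**The concern.** The quantity of interest is a difference between two scans of the same brain, taken a few weeks apart at most. Stable anatomy should cancel from that difference. It cancels fully only if the scans are segmented and warped consistently. If each scan finds its own way to a standard template, small differences in segmentation and warping between visits remain and look like change.

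The real-versus-sham comparison of changes uses four scans, so it carries four such errors. The stimulation course is five sessions and the later scan is on day eight, so any true structural change is likely to be small against this error. Regional volume change is also part of the mechanism that the article sets out to show (Abstract; Summary and conclusions). Because the structural result selects the connectivity seeds, noise there can drop relevant regions or make the seed set unstable.

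**Working it through.** **1. Text against text.** The article gives no power, SD or expected effect for volume or thickness, so there is no figure to reproduce. The main check sets the outcome against the steps.

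| What the outcome needs | What the steps name |
|---|---|
| Before/after scans of one patient in a common space | Manual alignment of each image to the commissures, which is to landmarks and not between scans |
| Consistent segmentation across visits | Segmentation, with no link between visits stated |
| Consistent warp to standard space across visits | Registration to a standard template, then MNI |
| The same for thickness | 15 mm smoothing, with between-subject comparability as the stated purpose |

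Elsewhere the article does spell out such operations. The fMRI paragraphs name realignment and coregistration (realignment there is to the first volume of the series, not between visits). The EEG section writes out the posttreatment-minus-baseline formula. The structural paragraphs have no counterpart.

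**2. How scan error enters the comparison.** For one region let

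D = (post − pre, real) − (post − pre, sham).

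Assume that each scan carries independent error with SD s, and that patients do not differ in their response. The patient's stable anatomy cancels, so

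Var(D) = s² + s² + s² + s² = 4s², and SD(D) = 2s.

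Error that is constant across a patient's scans cancels too, so s is only the part that varies from scan to scan.

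**3. Detectable change in units of s.** Detectable change = dz × 2s. Here dz is the standardised difference that gives 80% power at two-sided 0.05, from the noncentral t distribution with n − 2 degrees of freedom. The article sets that power and level for the motor endpoint; they are borrowed here. It also gives 21 as the required number, 24 enrolled, and about 20% drop-out, and 24 × 0.80 = 19.2, or about 19.

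| n | dz | Detectable change (2 × dz × s) |
|---|---|---|
| 24 | 0.598 | 1.20s |
| 21 | 0.645 | 1.29s |
| 19 | 0.682 | 1.36s |

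These are for a single region, before the multiplicity adjustment that Statistical analysis requires. At n = 21, assumed values of s of 0.5%, 1%, 2% and 3% of regional volume give 0.64%, 1.29%, 2.58% and 3.87%. None of these values of s is in the article.

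**4. What better processing could change.** Write s² = a² + p², with a for acquisition and day-to-day variation and p for processing. Reprocessing can reduce p only. If total error variance fell to 75%, 50% or 25% of its value (assumed), the n = 21 figure would be 1.289s multiplied by √0.75, √0.50 or √0.25, that is 1.12s, 0.91s or 0.64s. If patients also differ in response, with variance τ² on the scale of D, then SD(D) = √(4s² + τ²). The detectable change then falls by a smaller proportion than s does.

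**The case against.** The strongest reply is that this turns an omission into a method. A reader might infer that the trial has committed itself to a cross-sectional pipeline in which every scan is segmented and normalised independently. The article says neither. It refers to the toolbox manual, which is not at hand and might cover a longitudinal option. Most of the listed steps would also appear in a longitudinal workflow. The wording "smoothed with a 15 mm Gaussian kernel to allow intersubject comparisons" describes the purpose of smoothing, and a group analysis of change also needs comparability across patients. A journal article may leave such settings to the full protocol.

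Much of this stands: independent processing is inferred from what is not named. It does not remove the point. The volume paragraph is not a general pointer. It gives software, version, an ordered list and a kernel size, and that list goes from segmentation to a standard template with nothing between a patient's own scans. Someone following it would have no within-patient step.

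Three further readings are tempting and not supported. One is that a longitudinal pipeline would cut detectable change by some definite fraction. The article gives no scan-rescan error, part of s cannot be reduced, and response variation dilutes the gain. A second is that the real-versus-sham comparison is biased. With all scans processed alike the cost is precision. The third is that the trial's main conclusion is at risk. Volume and thickness are exploratory, the MDS-UPDRS outcome does not use them, and the independent component analysis of the fMRI data does not depend on structural seeds.

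**Conclusion.** The point holds in limited form. The outcome is short-term change within a patient, and the written steps for volume and thickness name no within-patient alignment. Followed as written, they let avoidable scan-to-scan processing error into each before/after difference and into the choice of connectivity seeds.

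The consequence is lower precision on exploratory outcomes. Its size cannot be set from the article. The multiples of about 1.2s, 1.3s and 1.4s at 24, 21 and 19 patients rest on independent per-scan error, no variation in response, and no multiplicity adjustment. The lower numbers are the more relevant ones, because the article expects drop-out and first removes patients with missing outcome data from each analysis. A change is worth making because a better-suited method exists for scans that are already planned.

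**What to change.** In Structural and resting-state functional MRI, specify within-patient longitudinal processing for both volume and thickness:

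1. Rigidly register each patient's T1 scans to that patient's own average.
2. Apply joint bias correction across those scans.
3. Segment the aligned scans.
4. Apply one shared within-patient deformation to MNI space, then smooth.

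State that the analysis is of real-minus-sham change. If the team already works this way, correcting the listed steps is enough.

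The cost is processing settings and computing time; no new scans or visits are needed. The downside is that scans already processed must be rerun. When the article was written, thirteen patients had been enrolled and four had undergone the crossover intervention, so that burden was still small.
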